### Sample size calculation

The sample size was calculated based on the comparison of cough resolution rate between the Tanreqing oral liquid group and the placebo group. According to the pilot study and expert consultations, the cough resolution rate for the Tanreqing oral liquid group and the placebo group was estimated as 80% and 40%, respectively, with a difference of 20% or higher considering clinically significant. According to the formula of $${n}_c=\frac{{\left({z}_{1-\alpha }+{z}_{1-\beta}\right)}^2}{{\left({\pi}_T-{\pi}_C-\Delta \right)}^2}\left[\frac{\pi_T\left(1-{\pi}_T\right)}{K}+{\pi}_C\left(1-{\pi}_C\right)\right]$$, where *π*_*T*_, *π*_*C*_ were the estimated cough resolution rate for the trial and placebo group of 0.8 and 0.4, respectively, Δ was the superior margin of 0.2, *α* of 0.025 was the one-sided 0.025 level of significance, *β* of 0.2 was the type II error, and the sample size of the placebo group was 63. According to the Tanreqing oral liquid group to placebo group ratio of 2:1, the sample size of the Tanreqing oral liquid group was 126.

According to regulatory requirements of a new 6th category oral drug of traditional Chinese medicine, the overall number of subjects in the Tanreqing oral liquid group should be no less than 300. Meanwhile, there are two independent clinical trials designed for different indications, i.e., AB and the common cold respectively to evaluate the efficacy and safety of Tanreqing oral liquid. Therefore, 300 subjects were divided into each indication equally to ensure that the overall subjects in Tanreqing oral liquid group would satisfy the regulatory requirement. Therefore, the total sample size was 225 (150/75 for the treatment and control group, respectively). Considering an expected post-randomization dropout rate of 20%, the sample size was set as 270, with 180 for Tanreqing oral liquid group and 90 for the placebo group.

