### Statistical analysis

The full analysis set (FAS) population will include all randomized participants who receive at least 20 mL trial medication and collect outcome data after treatment. It will be used to describe the analysis set which is as complete as possible and as close as possible to the intention-to-treat ideal of including all randomized participants. Per-protocol (PP) population will include all randomized patients who strictly follow the protocol. The safety set (SS) population will include all randomized participants who receive at least 20 mL trial medication and have safety evaluation data. Missing efficacy data will be imputed using the last observation carried forward method. Efficacy and safety analysis will be performed based on the FAS and PP population and SS population.

Statistical analysis will be performed using SAS 9.4 according to the statistical analysis plan. The primary outcome of cough resolution rate will be analyzed using the chi-squared or Fisher’s exact tests. Furthermore, logistic regression will be conducted to provide a risk ratio. For secondary outcomes, *t* test and nonparametric tests will be used for quantitative data, and chi-squared or Fisher’s exact tests will be used for qualitative data. A one-sided *P*-value of 0.025 or less will be considered statistically significant.

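### The plan takes a risk ratio from logistic regression, whose coefficient gives an odds ratio: 6 against a true risk ratio of 2 at the planned rates

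*Protocol article*

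**What the plan says.** The Statistical analysis section of the protocol article sets the test for the primary outcome: "The primary outcome of cough resolution rate will be analyzed using the chi-squared or Fisher’s exact tests". It then adds that "logistic regression will be conducted to provide a risk ratio". That risk ratio is the only effect measure the section names for the primary outcome. The section mentions no log link, no Poisson model and no standardisation of predicted risks. The term odds ratio does not occur anywhere in the article.

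The planning rates are in the Sample size calculation section: "the cough resolution rate for the Tanreqing oral liquid group and the placebo group was estimated as 80% and 40%, respectively". The same section sets a superiority margin on the difference of the two proportions ("was the superior margin of 0.2").

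**The concern.** A logistic model is linear in the log odds. Its exponentiated treatment coefficient is therefore the ratio of the odds of resolution, not the ratio of the probabilities. The odds ratio is close to the risk ratio only when the outcome is rare in both arms. Cough resolution is expected in 40% to 80% of patients, so the two will be far apart.

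An analyst who follows the sentence literally would fit the model, exponentiate the coefficient and report it as a risk ratio. Readers would take it as how many times more likely a patient is to resolve on Tanreqing than on placebo. The headline effect for the primary outcome would be exaggerated, and its confidence interval would be that of a different quantity. This matters the more because the trial is meant to support a new drug and the results are to go to participants, conferences and journals.

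**Working it through.** **Inputs** (Sample size calculation section): resolution rates π_T = 0.80 and π_C = 0.40; margin 0.20; α = 0.025 one-sided; β = 0.20; allocation 2:1; 180 and 90 patients to be randomised.

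**1. The protocol's own figure.** Its formula gives

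n_C = (1.960 + 0.842)² / (0.80 − 0.40 − 0.20)² × [0.80 × 0.20/2 + 0.40 × 0.60] = 7.849/0.04 × 0.32 = 62.79, rounded up to 63.

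This matches the stated 63 for placebo, so 80% and 40% are the rates the design rests on.

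**2. The two measures at the planned rates.**

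- Risk ratio = 0.80/0.40 = 2.0
- Odds ratio = (0.80/0.20)/(0.40/0.60) = 4/0.667 = 6.0
- Overstatement if the second is labelled as the first: 6.0/2.0 = 3. In general the factor is (1 − π_C)/(1 − π_T), here 0.60/0.20.

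**3. Confidence intervals at 180/90.** The planned rates give 144 resolved and 36 not on Tanreqing, 36 resolved and 54 not on placebo.

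- Odds ratio: SE of the log = √(1/144 + 1/36 + 1/36 + 1/54) = 0.285; 95% CI 3.43 to 10.48.
- Risk ratio: SE of the log = √(0.20/144 + 0.60/36) = 0.134; 95% CI 1.54 to 2.60.

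The intervals do not overlap. Models fitted to data with exactly these counts agree: logistic regression returns 6.00, log-binomial and robust-variance Poisson both return 2.00, and standardising the logistic predictions also returns 2.00.

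**4. Other treatment rates, placebo at 40%.**

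| Tanreqing | Risk ratio | Odds ratio | Factor |
|---|---|---|---|
| 60% | 1.50 | 2.25 | 1.5 |
| 70% | 1.75 | 3.50 | 2.0 |
| 80% | 2.00 | 6.00 | 3.0 |

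**5. A bound.** With 40% resolving on placebo, no risk ratio can exceed 1/0.40 = 2.5. A reported risk ratio of 6 would be impossible. At 60% against 40%, however, the mislabelled 2.25 lies below the bound and would not look wrong on its face.

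**The case against.** The strongest reply is that a logistic model can yield a valid risk ratio: standardise its predicted risks and the answer is 2.00, as shown above. The article refers to a statistical analysis plan that is not shown and may contain that step. A reported 6 is thus conditional on the usual coefficient being used. This stands as a limit on the forecast, but it does not clear the sentence. The article states a model and a measure that the model's coefficient does not give, and nothing in it links the two. That is a misstatement, not a detail left for later.

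Second, the logistic model is supplementary. The p-value comes from the chi-squared or Fisher test, and the sample size is built on the risk difference; neither changes. A reader given both arm rates could also work out the risk ratio. This is correct and confines the damage to the reported effect estimate and its interval.

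Third, the threefold figure belongs to the planned rates; at 60% against 40% the factor is 1.5. Also correct, though 1.5 is still a large overstatement. An odds ratio of 6 is not itself wrong; it misleads only when called a risk ratio.

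Fourth, recommending a risk difference goes beyond correcting the label. It does, and it is offered because the protocol's own margin is on that scale.

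**Conclusion.** The concern holds. As written, the plan attaches the name of one effect measure to a model whose coefficient estimates another, for an outcome common enough that they differ widely. At the planned 80% and 40%, a figure of 6.0 (95% CI 3.43 to 10.48 at 180/90) would stand in place of 2.0 (1.54 to 2.60).

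This size rests on two assumptions: that the observed rates are near the planned ones, and that the exponentiated coefficient is reported under the label the protocol gives it. The primary test and the sample size are sound on this point. The sentence should be corrected before results are reported.

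**What to change.** Replace the sentence with one that pairs model and measure correctly:

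- **To report a risk ratio:** use a log-binomial model, or a modified Poisson model with robust variance, or standardised predictions from the logistic model with a delta-method or bootstrap interval.
- **To keep plain logistic regression:** call its output an odds ratio.

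In either case, report the risk difference with a 95% CI as the main effect measure, so that the estimate can be read against the 0.20 margin.

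The cost is one sentence in the protocol and analysis plan and a different model call in SAS (PROC GENMOD); no new data are needed. Correcting the label alone should need little more. Making the risk difference the main measure might count as a significant change to the analysis, which under the article's Ethical considerations and dissemination section needs a signed modification and renewed ethics approval. It is best settled before unblinding.

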### Outcome measures

#### Primary outcome

Cough resolution rate: proportion of patients whose cough is completely resolved after treatment.

The overall frequency, severity, and impact of cough will be evaluated using a patient self-rated cough symptom score (CSS) scale. CSS scale will be graded twice daily at two intervals: daytime (from 8:00 am to 8:00 pm) and nighttime (from 8:00 pm to 8:00 am), each scored from 0 to 3 points [16]. Cough resolution will be defined as both daytime and nighttime CSS scale reduced to 0 without relapse for two consecutive days.

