#### Secondary outcomes

The following are the secondary outcomes:Change of bronchitis severity scores from baseline to post-treatment: Bronchitis severity score (BSS) is an observer-rated tool for assessing the severity of five major symptoms of AB including cough, sputum production, rales/rhonchi (auscultation), chest pain during coughing, and dyspnea, each rating from 0 to 4 points. The BSS is the sum of the five ratings ranging from 0 to 20 points [17].Cough relief rate: Cough relief will be defined as both daytime and nighttime CSS decreasing to 1 or less, or decreasing by 1 and lasting for two consecutive days. Cough relief rate will be the proportion of patients who achieve cough relief after treatment.Time to cough resolution: length of time at baseline to cough resolution: For example, the daytime and nighttime CSS on the patient’s diary cards on the 5th and 6th days are all 0 points, then the cough resolution time is recorded as “5 days.”Time to cough relief: Length of time at baseline to cough relief.Resolution rate of single TCM symptom.Combination medication use: Combination medication here will only include antibiotics, expectorants, and antitussives.Change of TCM syndrome score from baseline to post-treatment: Each TCM symptom will be graded (see Additional file 1). TCM syndrome score will be the sum of the main symptom score and all minor symptoms scores.Adverse events: Besides routine blood, urine, and stool tests and hepatic and renal functions, any unexpected symptom or sign during the treatment period will be recorded and analyzed.

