### Coordination and conduct of the trial

A multicenter trial coordination committee will be established and responsible for trial conduct. Data monitoring committee will not be established because (1) this trial will recruit AB participants and perform follow-up over a short period of 7 days, (2) pilot clinical observation found Tanreqing oral liquid was well tolerated and safety data from Tanreqing injection did not show any toxic potential in real-world cohorts [18], and (3) the primary outcome measure will be patients self-reported resolution of symptoms. Similarly, interim safety and efficacy analysis will not be conducted. An independent monitoring committee will conduct onsite monitoring monthly in accordance with the sponsor’s requirements and relevant regulations. An independent qualified auditor will randomly audit the trial to evaluate trial conduct and compliance with the protocol, good clinical practice, standard operating procedures, and the applicable regulations.

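### Time to cough resolution and time to cough relief are assigned to tests for complete quantitative data with no censoring rule, although about a third of patients are expected to have no resolution time

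*Protocol article*

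**What the plan says.** The Secondary outcomes section of the Protocol article lists two times, counted in days from the diary: "Time to cough resolution: length of time at baseline to cough resolution" and "Time to cough relief: Length of time at baseline to cough relief". Its worked example records a patient with zero scores on days 5 and 6 as resolved at 5 days. The Primary outcome section defines resolution as "both daytime and nighttime CSS scale reduced to 0 without relapse for two consecutive days". Relief is looser: "Cough relief will be defined as both daytime and nighttime CSS decreasing to 1 or less, or decreasing by 1", sustained for two days.

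The Statistical analysis section divides the secondary outcomes into two kinds. Qualitative data get chi-squared or Fisher's exact tests; for the rest, a *t* "test and nonparametric tests will be used for quantitative data". No survival method or censoring time is named. The one missing-data rule is: "Missing efficacy data will be imputed using the last observation carried forward method".

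Two further statements bear on the point. Coordination and conduct of the trial says that the trial will "perform follow-up over a short period of 7 days". Sample size calculation says that "the cough resolution rate for the Tanreqing oral liquid group and the placebo group was estimated as 80% and 40%, respectively", and it expects 20% dropout.

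**The concern.** A time in days is quantitative, so both time outcomes fall under the *t* test and nonparametric rule. That rule presupposes an observed value for each patient. A patient still coughing when the diary ends has no resolution time, only the knowledge that it is later than the last diary day. Carrying the last score forward does not help: it leaves the patient unresolved and yields no day.

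Someone must therefore decide what these patients contribute, and the stated rule does not say. Leaving them out selects on a post-randomisation outcome and removes mainly placebo failures. Entering day 7, or ranking them last, keeps the randomised groups but changes what is estimated. The reported number of days depends heavily on this choice.

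**Working it through.** **The plan's own figure.** The article states no figure for the time outcomes, so its sample size serves as a check on the inputs. With rates 0.8 and 0.4, margin 0.2, one-sided alpha 0.025, power 80% and K = 2:

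n_c = (1.960 + 0.842)² / (0.8 − 0.4 − 0.2)² × [0.8 × 0.2 / 2 + 0.4 × 0.6] = 7.849 / 0.04 × 0.32 = 62.8, rounded up to 63, with 126 on Tanreqing. This agrees with the article.

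**Patients without a resolution time.** Censored share = 1 − resolution rate.
- Tanreqing: 0.20 × 180 = 36
- Placebo: 0.60 × 90 = 54
- Total: 90 of 270, or 33%, three times as frequent on placebo

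Two zero days are required, so a zero first reached on day 7 cannot be confirmed within a 7-day diary. No relief rate is stated, so the same sum cannot be done for relief.

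**Log-rank power.** Under proportional hazards the ratio is ln(0.2) / ln(0.6) = 3.15. With 144 + 36 = 180 events and 2:1 allocation, z = √(180 × 2/3 × 1/3) × ln 3.15 − 1.96 = 6.32 × 1.148 − 1.96 = 5.30. With 120 + 30 = 150 events (150/75 patients), z = 4.67. Power exceeds 99.9% in both cases.

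**Size of the difference in days.** The documents give no time course, so its shape is an assumption: Weibull with S(t) = exp(ln(1 − p) × (t/7)^k), fixed to 80% and 40% resolved by day 7, with k = 1, 2 or 3. The restricted mean is the area under S(t) to day 7. For k = 1:
- Tanreqing: 0.8 / (1.609/7) = 3.48 days
- Placebo: 0.4 / (0.511/7) = 5.48 days
- Difference: 2.0 days

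For k = 2 and 3 the difference is 1.4 and 1.1 days. In simulation on whole diary days, the difference among resolvers only is about 0.6, 0.5 and 0.4 day, roughly a third of that. With non-resolvers set to day 7 it is about 1.8, 1.2 and 0.9 days, whereas the uncapped mean differences are 9.4, 3.8 and 2.5 days.

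**Power (%), 2,000 simulated trials per row, one-sided 0.025, rates 80% and 40%.**

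| Scenario | n | Log-rank | Resolvers only, *t* | Resolvers only, Wilcoxon | Day 7 entered, *t* | Ranked last, Wilcoxon |
|---|---|---|---|---|---|---|
| k = 1 | 180/90 | 100 | 37.3 | 35.5 | 100 | 100 |
| k = 2 | 180/90 | 100 | 34.9 | 35.6 | 100 | 100 |
| k = 3 | 180/90 | 100 | 32.6 | 35.5 | 99.95 | 100 |
| k = 1 | 150/75 | 100 | 33.5 | 31.3 | 99.95 | 100 |
| k = 2 | 150/75 | 100 | 30.2 | 30.6 | 99.95 | 100 |
| k = 3 | 150/75 | 100 | 26.0 | 28.0 | 99.6 | 100 |
| Same timing among resolvers | 180/90 | 100 | 2.0 | 2.1 | 99.2 | 99.95 |
| Same timing among resolvers | 150/75 | 100 | 3.8 | 3.7 | 98.5 | 99.95 |

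A 6-day window for k = 2 at 180/90 gives the same picture (resolvers-only *t* test 35.8%). With a smaller effect of 60% against 40% (k = 2, 150/75), power is 82% for log-rank, 7.6% for the resolvers-only *t* test, 65% with day 7 entered and 82% with non-resolvers ranked last. With 40% in both arms, every method rejects in about 2.5% of trials.

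**The case against.** The strongest reply is that the harm depends on a handling the article does not state. Nothing says that non-resolvers are dropped. With one common 7-day cut-off, a rank test needs only an ordering, and tying unresolved completers at the worst rank is a valid randomised comparison. At the planned rates it is nearly as efficient as log-rank (mean z about 6.2 against 6.4 at 180/90). Entering day 7 for completers gives a restricted mean with an ordinary standard error. The word nonparametric could cover a log-rank test, and the analysis plan that the article refers to is not shown.

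Much of this stands, and it rules out three stronger readings that a reader might reach.
- That the comparison is certainly biased and loses nearly all its information. Near-total loss (power of 2-4%) needs non-resolvers to be dropped and resolvers in both arms to have the same timing; the article states neither.
- That 20% and 60% are censored for relief as well. Those figures come from the resolution rates, relief is easier to reach, and no relief rate is given.
- That entering day 7 is wrong in itself. For completers it is a legitimate estimand, provided it is reported as a restricted mean.

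The reply does not remove the point. The article is not silent here: it states a method for every secondary outcome, and a *t* test on days does not fit censored times. Paired with the *t* test and tied to quantitative data, nonparametric most naturally means a rank test on complete values. The day-7 and worst-rank defences also cover completers only; with 20% dropout expected, patients who leave early without the event have no assigned time or rank.

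**Conclusion.** The point holds as a mismatch between two secondary outcomes and the tests assigned to them. About 90 of 270 patients (20% and 60% by arm) are expected to have no resolution time, and no stated rule handles them. The figure for relief is unknown and probably lower.

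The size of the harm is conditional. Dropping non-resolvers gives a non-randomised comparison that recovers about 0.4-0.6 day of a 1.1-2.0 day restricted-mean difference, with about 26-37% power under proportional hazards. Entering day 7 or ranking them last keeps power at 98% or more at the planned rates, but yields a restricted mean or a rank comparison and should not be read as a mean time to resolution. The counts follow from the article; the days and simulated power also rest on the assumed Weibull shapes. The null simulation showed no inflation of type I error, and the primary chi-squared analysis is untouched. The wording should be corrected; the design is not at risk.

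**What to change.** In the Statistical analysis section, take both time outcomes out of the rule for quantitative data and analyse them as time-to-event:
- Kaplan-Meier curves, a log-rank test stratified by the randomisation strata, and a Cox or discrete-time hazard ratio with 95% confidence interval.
- Patients who complete without the event censored at the end of the 7-day diary.
- A stated censoring rule for early dropouts. Censoring of patients withdrawn for worsening is informative, so add a sensitivity analysis that treats them as unresolved through day 7.
- Optionally, the restricted mean to day 7 as a summary in days, labelled as such.

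If the analysis plan already specifies this, only the article's sentence needs correcting. The cost is wording and standard SAS procedures; the daily diary already records the cough scores, so no new data are needed.

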### Ethical considerations and dissemination

Each study center will designate a research assistant to recruit patients from respiratory outpatients or emergency departments. After approval of the ethics committee, if there are significant changes to eligibility criteria, outcomes, and data analyses, the primary investigator will write and sign the “protocol modification specification,” and report to the Ethics Committee for approval again before implementation. Trained research investigators will explain detailed information regarding the study aim, potential benefits and risks, alternative treatment options, and patients’ rights and obligations to potential participants prior to participation. After obtaining voluntarily signed informed consent from participants, the research investigators will arrange some physical and laboratory examinations according to the study procedure to confirm whether participants really meet the inclusion and exclusion criteria. Then, research investigators will give a detailed introduction of the study protocol and study procedures to all eligible participants. Participants who might have difficulty in weighing the risks and benefits of the study will be excluded from this study. All participants will be free to refuse to take part in the trial and drop out of the trial during the process at any time. If patients who comply with the trial protocol suffer from any AE and need to be treated, the investigators will provide timely and effective therapy options and perform follow-ups until patients reach a complete resolution. Moreover, only researchers, monitors, drug regulatory departments, and ethics committee have access to participants’ personal medical records. Data processing will omit the information that can identify the individual identity. Each participant will be identified only with a unique subject identity never be disclosed to anyone in the result dissemination and publication.

The primary investigators and sponsor will communicate the trial results to participants and all the investigators involved. The trial results will be submitted to national or international conferences or peer-reviewed journals with the sponsor’s permission.

